### Intervention: cognitive behaviour therapy for FCR

The intervention was developed as face-to-face CBT with access to a website that provides online materials and the option to engage in therapist-patient interaction. For the therapists, a structured manual with a detailed description of each therapy session has been developed. The CBT covers 3 months and comprises five individual one-hour face-to-face sessions (session 1, 2, 3, 5 and 8) and three (15 minutes) e-consults or telephonic consultations (session 4, 6 and 7). In order to sustain behaviour change and monitor therapy progress, patients will be invited for a booster session at 3-month follow-up.

Intervention components were partially based on existing traditional CBT models for health anxiety and generalised anxiety. As with other forms of CBT, the primary emphasis of the therapy is on perpetuating factors of the problem in question. In this case, those factors maintaining high FCR. The principal therapeutic techniques are self-monitoring, cognitive restructuring (identification and re-attribution of unhelpful thoughts) and exposure- and response prevention. Other techniques are psychoeducation, relaxation, mindfulness, reframing, modelling (patient videos), at-home assignments, goal planning and attainment (Marks et al. 2011). The first session is directed at case conceptualisation and formulation of a personal FCR model, taking into account personal characteristics, triggers of fear, cognitions and consequences of FCR (see Figure 1). The FCR model guides the course of therapy by identifying the most appropriate points or targets for intervention (e.g. unhelpful cognitions). It is open to modification in the course of therapy because new insights might require adjustments in certain parts of the FCR model. The following four sessions (session 2 to 5) focus on acceptance, on identifying/modifying dysfunctional thinking patterns and on behaviour modification. If desired by patient or therapist, spouses will be invited to attend one or more therapy sessions. The final three sessions (session 6 to 8) are directed at consolidation of therapy progress and the establishment of a relapse prevention plan. Self-management skills are reinforced and active contribution to therapy progress and goal setting is encouraged. Completion of at-home assignments is of pivotal importance in order to practice the skills learned during therapy and to establish enduring change. A more detailed description of the intervention by session is described in Table 1.

**Table 1 Tab1:** **Content of the intervention by therapy session**

**Session**	**Delivery**	**Week**	**Time (minutes)**	**Session components**
1	Face-to-face	1	90	• Case formulation: a patient’s story.
				• Discuss therapy rationale.
				• Establish therapy goals.
				• Review FCR and complete a personal FCR model.
				• Introduce at-home assignments.
2	Face-to-face	2	60	• Explain the basic tenets of CBT.
				• Discuss and visualize the association between thoughts, feelings and actions.
				• Review the concept of helpful beliefs.
				• Practice in filling out thought records.
				• Introduce mindfulness and relaxation exercises.
3	Face-to-face	3	60	• Review the completed thought record(s) to identify unhelpful thoughts and behavioural consequences of FCR.
				• Differentiate realistic from unrealistic worries and establish more helpful thoughts.
				• Explore and identify dysfunctional behavioural patterns.
				• Create a ranked list of situations that induce FCR and propose a behavioural experiment.
				• Practice a mindfulness or relaxation exercise.
4	E-consult (or telephone)	4	15	• Review of progress (troubleshooting).
				• Encourage at-home skill practice.
5	Face-to-face	6	60	• Review therapy goals, discuss areas of concern and make future plans (beyond therapy).
				• Discuss completed thought records and/or behavioural experiments.
				• Identify personal strengths and resources of strength.
6	E-consult (or telephone)	7	15	• Review of progress (troubleshooting).
				• Encourage at-home practice of skills.
7	E-consult (or telephone)	9	15	• Review of progress (troubleshooting).
				• Introduce the relapse prevention plan.
8	Face-to-face	11	60	• Review therapy goals, progress made so far and discuss possible future pitfalls.
				• Define and finalize the relapse prevention plan.
				• Evaluate the therapy process.
				• Schedule an appointment for the booster session.
9	Face-to-face (booster session)	24	60	• Review the FCR model and progress made during therapy.
				• Discuss difficult situations and how to overcome them.
				• Relapse prevention plan.

### Control condition: treatment as usual

Cancer survivors in the control condition have access to TAU and will not be offered additional psychological therapy for managing FCR. This condition reflects the natural course of FCR over time and gives insight in the standard care practices that are offered to persons outside the study context (e.g. during routine medical follow-up). In the period after cancer treatment all patients are offered medical follow-up appointments conform the recommendations of the Dutch guidelines in oncology care (Comprehensive Cancer Centre the Netherlands 2011). For colorectal cancer, the Dutch guideline advises medical examinations every 6 months during the first 2 years of follow-up, continued by yearly examinations up to 5-years follow up. For breast cancer, the Dutch guideline advises medical follow-up examinations every 3 months during the first year, every 6 months during the second year and examinations once a year during 2 to 5 years follow-up. For prostate cancer, during the first year after cancer treatment a follow-up schedule of 6 weeks, 3, 6, 9 and 12 months is recommended, and semi-annually or annually thereafter for 5 to 10 years. In the Netherlands, psychosocial follow-up is not institutionalised and psychosocial care offered to cancer survivors with high FCR therefore differs between health care institutions. Information on additional medical or psychosocial care survivors have had during the study period will be collected for both the interventions and the control group. This includes utilization of psychosocial services (e.g. psychological therapy, mindfulness and social work), health care consultations (e.g. GP, medical specialists, and paramedical assistance) or medication use.

### Participating therapists

All CBT sessions will take place at the RUMC, department of Medical Psychology in Nijmegen, the Netherlands. The CBT will be practiced by two qualified, registered healthcare psychologists with experience in delivering CBT for somatic conditions and experience in the field of psychosocial oncology. During the study, both therapists will have regular supervision by a registered clinical psychologist, also qualified as CBT supervisor [name]. Before the start of the study, both therapists had already performed one supervised treatment case conform the therapy manual.

### Treatment integrity

To be able to draw valid conclusions on the therapy effects, treatment integrity (e.g. the implementation of the treatment as intended) is ensured conform the guidelines established by the Behaviour Change Consortium (Bellg et al. 2004), i.e. with the use of a standardised therapy manual and ongoing therapist supervision. All sessions will be audio taped and 5% will be randomly checked for adequate therapy implementation.

### Outcomes

Detailed information on the study outcomes is available in Table 2. Participants will be asked to complete questionnaires at four different time points, either online or on paper. Demographic and medical information will be gathered with self-report questionnaires and from medical records.

**Table 2 Tab2:** **Primary and secondary outcome measures of the SWORD-study**

**Primary outcome**				
	**Questionnaire**	**Response format**	**Example question**	**Timepoints**
**Fear of cancer recurrence**	Cancer Worry Scale (CWS) (8 items)	4-point Likert scale *range 8 - 32	*During the past month: “How often have you thought about your chances of getting cancer (again)?”*	Screening T0;T1;T2;T3
**Secondary outcomes**				
**Dimensions of FCR**	Fear of Cancer Recurrence Inventory (42-items)	5-point Likert scale	*“How many times per day do you spend thinking about the possible chance of recurrence?” “I am worried or anxious about a possible chance of recurrence.” “I try to replace this thought with a more pleasant one.”*	T0;T1;T2;T3
	Subscales:			
	• Triggers (8 items)	−0 - 32		
	• Severity (9 items)	−0 - 36		
	• Psychological distress (4 items)	−0 - 16		
	• Functional impairment (6 items)	−0 - 24		
	• Coping strategies (9-items)	−0 - 36		
	• Insight (3 items)	−0 - 12		
	• Reassurance Seeking (3 items)	−0 - 12		
**Cancer related quality of life**	EORTC-QLC C30 (30 items) Subscales:	4-point Likert scale	*“Were you limited in pursuing your hobbies or other leisure time activities?” “How would you rate your overall health during the past week? (Global health)”*	T0;T1;T2;T3
	• Five functional scales (15 items)	−15 - 60		
	• Three symptom scales (7 items)	−7 - 28		
	• Single symptom items (6 items)	−6 - 24		
	• Global health & quality of life scales (2 items)	−2 - 14		
**Cancer specific quality of life: Breast cancer**	EORTC-BR23 (23 items) Four functional scales (8 items)	−8 - 32	*“Have you felt physically less attractive as a result of your disease or treatment?”*	T0;T1;T2;T3
	• Four symptom scales (15 items)	−15 - 60		
**Cancer specific quality of life: Prostate cancer**	EORTC-PR25 (25 items)		*“Have you had difficulty going out of the house because you needed to be close to a toilet?”*	T0;T1;T2;T3
	• Two functional scales (6 items)	−6 - 24		
	• Four symptom scales (19 items)	−19 - 76		
**Cancer specific quality of life: Colorectal cancer**	EORTC-CR38 (38 items) Two functional scales (7 items)	−7 - 28	*“During past week, where you bothered by gas (flatulence)?”*	T0;T1;T2;T3
	• Seven symptom scales (28 items)	−26 - 104		
	• Three single symptom items	−1 - 4		
**Satisfaction with life**	Satisfaction With Life Scale (5-items)	7-point Likert scale *5 - 35	*“In general, I am satisfied with life.”*	T0;T1;T2;T3
**Distress**	Hospital Anxiety and Depression Scale (14 items) Subscales	4-point Likert scale *0 - 42	*“I feel tense or wound up” “I feel as if I am slowed down”*	T0;T1;T2;T3
	• Anxiety (7 items)	−0 - 21		
	• Depression (7 items)	−0 - 21		
	Distress thermometer (1 item) Problem List (47 items)	VAS *0 - 10 *0 - 47	*“Circle the number (0-10) that best describes how much distress you have been experiencing in the past week.”*	T0;T1;T2;T3
**Fatigue severity**	Checklist Individual Strength – Fatigue Severity subscale (8 items)	7-point Likert scale *8 - 56	*“I feel tired” “I am rested”*	T0;T1;T2;T3
**Optimism**	Life orientation Test (LOT) (12 items)	5-point likert scale *0 - 32	*“In uncertain times, I usually expect the best.”*	T0;T1;T2;T3
**Body vigilance**	Body Vigilance Scale (4-items)	VAS scale *0 - 10 item 1-3 *0 - 15 item 4	*“I am very sensitive to changes in my internal bodily sensations”*	T0;T1;T2;T3
**Coping with the experience of cancer**	Impact of Events Scale (15 items) Subscales	4-point Likert scale *0 - 35 *0 - 40	*“Any reminder brought back feelings about it.” (intrusion)*	T0;T1;T2;T3
	• Intrusion (7 items)			
	• Avoidance (8 items)			
**Perceived social support**	Social Support List – Dissatisfaction scale (34-item)	4-point likert scale *34 - 102	*What is your opinion about the extent to which people…: “Drop in for a pleasant visit?”*	T0;T1;T2;T3
**Personality**	Big Five Inventory (44 items) Subscales Neuroticism (8 items)	5-point Likert scale	I see myself as someone: *“Who… can be somewhat careless.” (conscientiousness) “Who… Is sometimes shy, inhibited.” (extraversion*)	T0
	• Extraversion (8 items)			
	• Openness (10 items)			
	• Conscientiousness (9 items)			
	• Agreeableness (9 items)			
**Health care use**	EQ-5D (5 items) EQ-5D thermometer	4-point Likert scale VAS Scale (0 - 100)	*“Please indicate which statement best describes your own health state today.”*	T0;T1;T2;T3
	TIC-P – part I	Open ended questions	*In the past 4 weeks did you “how often did you visit the general practitioner?”*	T0
	Custom made cost diaries	Open ended questions	*During the specified period: ‘How often did you consult the general practitioner and why?’*	Between T0-T1 T1-T2 T2-T3 T3-T4

### Screening and primary outcome

Participants will be screened on high *Fear of cancer recurrence* with the Cancer Worry Scale (CWS). This questionnaire is validated as a screening instrument and is able to detect high FCR in Dutch cancer survivors (Custers et al. 2014). A cut-off score of ≥ 14 appeared optimal for differentiating high fearful patients from non-fearful patients. The CWS has good psychometric properties (α = 0.87).

### Secondary outcomes

*Multidimensional aspects of FCR* will be assessed with the Fear of Cancer Recurrence Inventory (FCRI). The FCRI gives a global idea of FCR in the preceding month and provides information about the principal characteristics of FCR (e.g. fear invoking stimuli/situations). The FCRI consists of 7 subscales; Triggers, Severity, Psychological distress, Coping strategies, Functioning Impairments, Insight, and Reassurance (Simard & Savard 2009).

*Quality of Life* will be measured with the Dutch version of the European Organization for Research and Treatment of Cancer (EORTC) Quality of Life Questionnaire Core 30 (QLQ-C30). Complementary to the QLQ-C30, disease specific modules for breast cancer (QLQ-BR23), colorectal cancer (QLQ-CR38) and prostate cancer (QLQ-PR25) will be assessed (Aaronson et al. 1993). Both the EORTC-QLQ-C30 and the disease specific modules have demonstrated moderate to good psychometric properties and clinical validity in cancer survivors (Aaronson et al. 1993; Sprangers et al. 1996; Sprangers et al. 1999; van Andel et al. 2008).

*Satisfaction with life* will be evaluated with the Satisfaction With Life Scale (SWLS). The SWLS has sufficient psychometric properties (α = .87) and is able to detect changes in life satisfaction over time (Diener et al. 1985).

*Distress* will be measured with the Hospital Anxiety and Depression Scale (HADS) total score (Annunziata et al. 2011; Vodermaier & Millman 2011). In addition, the Dutch version of the Distress Thermometer (DT) and the problem list will be completed as well (Tuinman et al. 2008).

*Fatigue* severity will be assessed with the fatigue severity subscale of the Checklist Individual Strength (CIS-8R) (Dittner et al. 2004; Servaes et al. 2002).

*Bodily vigilance* refers to the tendency to focus on internal bodily sensations and will be assessed with the four-item Body Vigilance Scale (Schmidt et al. 1997).

*Coping with the experience of cancer* will be measured with the Impact of Events Scale. This scale consists of 15 items that ask for the frequency of cancer-related avoidant and intrusive cognitions or behaviours (Horowitz et al. 1979) .

*Perceived social support,* or rather the perceived discrepancy between a patient’s desired social support and the actual amount of social support received, will be assessed with the Social Support List – Dissatisfaction (SSL-D) scale (Van Sonderen & Ormel 1997).

*Personality* dimensions will be measured with the Big Five Inventory (BFI) (Denissen et al. 2008). This is a 44-item multidimensional personality inventory that covers the five main dimensions of personality trait (conscientiousness, agreeableness, emotional stability, extroversion and intellect or openness (John & Srivastava 1999)).The BFI will only be administered at baseline (T0).

*Optimism*, as a dispositional trait, will be assessed with the Life Orientation Test (LOT). This questionnaire contains twelve items on the optimistic and pessimistic trait of personality (Scheier & Carver 1985).

*Health Care Use/cost-effectiveness:* The EuroQol-5D (EQ-5D) will be used to calculate *cost-utility.* It has shown to be an appropriate measure for economic evaluations in health interventions with breast cancer patients after treatment (Kimman et al. 2009). The instrument is able to detect changes in patients’ self-reported health related quality of life and has good psychometric properties (Kimman et al. 2009; Ravens-Sieberer 2010). *Health care costs* will be further monitored with cost diaries and the Trimbos/iMTA Costs associated with Psychiatric Illness (TiC-P) questionnaire (Hakkaart-Van Roijen 2002). Patients will be asked to report both direct health care costs (e.g. use of health care services, change of prescribed medication) and indirect costs (e.g. absence from work) during specified time periods (see Table 2).

### Technical usage statistics (intervention condition only)

Website use and completion of exercises can be seen as a form of treatment adherence. This includes data on number of exercises completed, frequency of logins, time online and webpages opened (Donkin et al. 2011). Technical data for those using the workbook will include the number of exercises completed.

### Intended statistical analyses

SPSS will be used for all statistical analyses. All statistical tests will be two-sided (level of significance = 0.05). To ensure that the key variables are evenly distributed by randomisation, baseline characteristics will be compared between the two conditions with Chi-square (categorical variables) and ANOVA (continuous variables) testing. Primary efficacy analysis will be conducted in agreement with the intention-to-treat principle. Additionally, a per-protocol analysis will be conducted using the data for those who successfully completed the intervention. Differences between the two conditions in the amount of change in FCR (T0 and T1) will be calculated with ANCOVA-analysis. Later, the follow-up effects (T3, T4) will be investigated with longitudinal data analysis. Next to statistical significance the clinically significant improvement will be established according to the method by Jacobson & Truax, calculating the reliable change index (Jacobsen & Truax 1984).

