**Methods/design:**

The SWORD-study has a randomised controlled design with two arms. A sample of 104 high fearful cancer survivors (breast, prostate or colorectal cancer) will be recruited from local hospitals. Cancer survivors will be randomised to receive CBT (intervention condition) or treatment as usual (control condition). For those in the intervention condition, the therapy will be individually delivered in a combination of 5 face-to-face therapy sessions and 3 online or telephone sessions by a trained therapist. Furthermore, these survivors will have access to a supportive website (or workbook) throughout the therapy. Survivors in the control condition will not receive the intervention and will not have access to the website. The primary outcome will be severity of fear of recurrence (Cancer Worry Scale). Quality of life (EORTC Quality of Life Questionnaire Core 30) and general psychological wellbeing will be assessed as secondary outcomes. Assessments will take place at baseline (before random assignment), at 3, 9 and 15 months after the baseline assessment. The study has been approved by an ethical review board.

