### Sample size

The sample size is calculated for the primary outcome FCR as measured with the Cancer Worry Scale (Custers et al. 2014). To detect a medium difference in FCR (Cohen’s d = 0.50), with a two-sided type I error rate of 0.05 and a power of .80, a sample size of 128 patients is needed. To correct for the baseline measurement as covariate the sample size is multiplied with the factor (1-r^2^), where r denotes the correlation between the baseline and post-intervention FCR (0.6 based on preliminary research) (Heinrichs et al. 2012). Therefore, a total sample size of 82 patients is desired. Because of an anticipated attrition rate of 20%, 52 patients are required per condition (104 total) (Lebel et al. 2014).

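### The additional per-protocol analysis selects completers in the CBT arm only, so it would compare self-selected CBT patients with unselected controls

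*Protocol article*

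**What the plan says.** Under Intended statistical analyses, the protocol article first sets the main analysis: "Primary efficacy analysis will be conducted in agreement with the intention-to-treat principle". It then adds that "a per-protocol analysis will be conducted using the data for those who successfully completed the intervention". The between-arm method for the post-treatment assessment is given in the same paragraph: "Differences between the two conditions in the amount of change in FCR (T0 and T1) will be calculated with ANCOVA-analysis".

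On the control arm, the Abstract (Methods/design) says: "Survivors in the control condition will not receive the intervention and will not have access to the website". The section on the control condition says that these patients "have access to TAU and will not be offered additional psychological therapy for managing FCR". Website use and exercise completion, which the article treats as a form of adherence, are recorded in the intervention condition only.

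The article does not say what makes completion successful, which controls enter the per-protocol set, or whether selection into completion will be adjusted for.

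**The concern.** A per-protocol set defined by finishing the therapy depends on something that happens after randomisation and can happen in one arm only. Read literally, the set contains no controls at all. The one reading that allows a comparison between conditions is CBT completers against the whole control arm. That comparison is no longer randomised: the CBT side has lost its non-completers, while their counterparts among the controls, whom nobody can identify, stay in.

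Selection on prognosis is plausible here. Completion means repeated visits to a single centre, exposure work and regular home assignments. Patients who persist may differ in motivation and outlook from those who stop. The word *successfully* is undefined, so membership might even be judged partly on response to therapy.

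At stake is how a result in completers is interpreted. It could be quoted as the effect of CBT in those who received it when part of it reflects who stayed.

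**Working it through.** **The plan's own figure.** The sample size reproduces and is not in dispute. A two-sample t-test with d = 0.50, two-sided 0.05 and power 0.80 needs 63.77, so 64 per arm, or 128 in total. Then 128 × (1 − 0.6²) = 128 × 0.64 = 81.92, so 82, or 41 per arm. Finally 41 / 0.80 = 51.25, so 52 per arm, or 104 in total.

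**Inputs for the bias illustration**
- From the Sample size section: baseline to post-treatment correlation r = 0.6; target effect d = 0.50; 52 per arm.
- Assumed, not in the article: no true CBT effect; all 52 controls analysed; a proportion c of the CBT arm completes, with c = 0.80 as the central case; completion follows a normal latent variable that correlates ρ with a better baseline-adjusted outcome. The article's 20% is anticipated attrition, not a rate of therapy non-completion.

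**Formulae**
- SD left after adjusting for baseline: √(1 − 0.6²) = 0.8 of the raw SD. Baseline ANCOVA thus leaves 64% of the outcome variance open to selection.
- Mean of the latent variable among those retained: λ = φ(z)/c, with z the (1 − c) quantile. For c = 0.80, z = −0.842 and λ = 0.350.
- Spurious benefit in raw SD: ρ × λ × 0.8.
- Standard error in residual SD units with 52 controls and 52 × 0.80 = 41.6 completers: √(1/52 + 1/41.6) = 0.208.

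**Results at 80% completion**

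| ρ | Bias (raw SD) | Share of the 0.50 target | False-positive rate (nominal 5%) |
|---|---|---|---|
| 0 | 0 | 0% | 5.0% |
| 0.1 | 0.1 × 0.350 × 0.8 = 0.03 | 6% | 5.3% |
| 0.3 | 0.3 × 0.350 × 0.8 = 0.08 | 17% | 8.0% |
| 0.5 | 0.5 × 0.350 × 0.8 = 0.14 | 28% | 13.4% |

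For completion between 70% and 90% and ρ between 0.1 and 0.5, the bias runs from about 0.02 to 0.20 SD and the false-positive rate from about 5% to 21%.

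**The alternative estimator.** Controls have no access to this CBT, so non-compliance is one-sided and the complier average causal effect is essentially the intention-to-treat effect divided by c. In residual SD units its standard error is roughly √(2/52) / 0.80 = 0.196 / 0.80 = 0.245. That is 0.245 / 0.208 = 1.18 times that of the naive comparison.

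It assumes that non-completers gain nothing. If completers gained 0.50 and the 20% who stop early gained 0.25 (both assumed), the intention-to-treat effect would be 0.8 × 0.50 + 0.2 × 0.25 = 0.45. The estimate would then be 0.45 / 0.8 = 0.56, which is 12.5% too large.

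**The case against.** The strongest reply is about weight. The analysis is additional, the primary analysis is intention-to-treat, and neither the sample size nor the efficacy conclusion depends on the completer result. That stands, and it limits the point to a supportive analysis.

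Second, the comparator is inferred. The article does not say that all controls enter, and a fuller plan may set a completion threshold or a control-side rule. The absence of those details is not the criticism. The stated principle, selecting on completion, is. No control-side rule makes the arms comparable, because nobody can observe which controls would have completed CBT.

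Third, size and direction are not known. A reader might infer that the analysis will show a benefit even if CBT does nothing. The article does not support that: it gives no link between completion and outcome, the bias vanishes at zero correlation and is small at 0.1, and it would reverse if patients who improve early are the ones who stop.

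A reader might also infer from Table 1, which numbers the week-24 booster as session 9, that completion includes it. Membership of the T1 analysis (about week 13) would then be decided some 11 weeks after T1. The rest of the article points the other way. The Abstract counts five face-to-face and three remote sessions. Trial design places the CBT between the first two assessments. The intervention section gives the therapy as eight sessions over 3 months and describes the booster separately. The session 8 entry "Schedule an appointment for the booster session" says nothing about a completion criterion.

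Finally, the complier estimate is largely the intention-to-treat effect rescaled and needs an assumption that partial therapy may breach. That is a fair caution and belongs in the fix.

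**Conclusion.** The point holds as a defect of the additional per-protocol analysis, and it should be corrected. The selection rule can act on the CBT arm only and gives up the protection of randomisation. The primary intention-to-treat result is untouched.

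The completer comparison can show a spurious benefit if completers have the better prognosis. With no true effect and 80% completion, this is 0.03 to 0.14 SD for correlations of 0.1 to 0.5. These figures rest on an assumed completion rate, assumed correlations and a normal selection model. They show what could happen and do not predict what this trial will find.

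**What to change.** Change the analysis wording before outcome data are seen:

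1. Define completion by attendance at the eight CBT sessions, with the threshold fixed in advance and no reference to therapy response or questionnaire scores.
2. Estimate the effect in completers as a complier average causal effect, with randomised allocation as instrument for completion (two-stage least squares), adjusted for baseline Cancer Worry Scale score and cancer type.
3. State the exclusion restriction, namely that allocation to CBT changes nothing in patients who do not complete. Repeat the analysis with a lower attendance threshold as a sensitivity analysis, since those still classed as non-completers will then have had less therapy.
4. If CBT completers are still compared with all controls, label the comparison descriptive.

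No new data collection is needed beyond session attendance. The cost is a confidence interval about 18% wider than that of the naive comparison (at 80% completion, under the assumptions above) and an estimate that is too large if partial therapy helps.

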### Randomisation

After completion of baseline assessment survivors will be allocated to CBT or TAU according to a computer generated randomisation list, with a 1:1 allocation ratio using a fixed block size of six participants. Stratification by cancer type (breast, colorectal and prostate cancer) will be applied Randomisation is computerised, using a randomisation website specifically designed for this study. An independent secretary will enter all necessary patient data into the programme and will communicate the randomisation outcome (CBT or TAU) to the researcher who further informs the study participant. Cancer survivors allocated to the CBT condition will be assigned to one of two therapists according to therapist availability.

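### Randomisation is stratified by cancer type, but the only adjustment described for the primary ANCOVA is baseline CWS; separately, baseline significance tests are planned to ensure balance, which they cannot do.

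*Protocol article*

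**What the plan says.** - **Randomisation:** allocation is 1:1 in fixed blocks of six. "Stratification by cancer type (breast, colorectal and prostate cancer) will be applied".
- **Intended statistical analyses, primary analysis:** "Differences between the two conditions in the amount of change in FCR (T0 and T1) will be calculated with ANCOVA-analysis". No covariates are listed in this section.
- **Sample size:** "To correct for the baseline measurement as covariate the sample size is multiplied with the factor" (1 − r²), with r = 0.6. This is the only place where the article names a covariate for the primary comparison.
- **Intended statistical analyses, baseline:** "To ensure that the key variables are evenly distributed by randomisation, baseline characteristics will be compared between the two conditions", by chi-square tests for categorical variables and ANOVA for continuous ones. The section sets a general two-sided level of 0.05. It does not say what follows from a significant result.

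Cancer type appears in the eligibility criteria, the stratification and the choice of disease-specific questionnaires, but in no described analysis.

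**The concern.** Stratified blocks balance the arms on cancer type, so the treatment estimate varies less from one randomisation to another wherever cancer type is related to outcome. A model without cancer type does not recognise this: the between-cancer variation stays in the residual, and the reported standard error exceeds the true one. Intervals are then too wide and the test is conservative. The article itself gives a reason to think that cancer type could matter. Its Discussion assumes that men and women handle emotional problems differently, and it presents the three cancers as male, female and mixed-gender groups.

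The baseline tests are a separate matter. Allocation comes from a computer-generated list, so with correct randomisation any difference between the arms at baseline is due to chance. A p-value then cannot ensure balance: a significant result flags chance, and a non-significant one with 52 per arm does not show that the arms are alike on a prognostic variable.

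**Working it through.** **1. The plan's own sample size reproduces.** Inputs, all from the Sample size section: d = 0.50, "with a two-sided type I error rate of 0.05 and a power of .80", r = 0.6 and 20% attrition.

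- The noncentral t gives 64 per arm, 128 in total, as stated (the normal approximation gives 63 per arm, 126).
- 128 × (1 − 0.6²) = 128 × 0.64 = 81.92, so 82, or 41 per arm.
- 41 / (1 − 0.20) = 51.25, so 52 per arm, 104 in total.

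With residual SD √(1 − 0.36) = 0.80, the standard error is 0.80 × √(2/41) = 0.1767. Power is Φ(0.5/0.1767 − 1.96) = 0.808 (normal approximation).

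**2. Effect of omitting cancer type.** Let R2 be the share of T1 CWS variance left after baseline CWS that cancer type explains. The documents give no value, so 0 to 0.10 is an assumption. With the arms balanced within cancer type:

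- true SE = 0.1767 × √(1 − R2), while the model without cancer type reports about 0.1767; ratio 1/√(1 − R2)
- type I error without adjustment = 2 × [1 − Φ(1.96/√(1 − R2))]
- power without adjustment = Φ(0.5/true SE − 1.96/√(1 − R2))
- power with adjustment = Φ(0.5/true SE − 1.96)

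| Assumed R2 | SE too large by | Type I error, unadjusted | Power, unadjusted | Power, adjusted |
|---|---|---|---|---|
| 0 | 0% | 0.0500 | 0.8078 | 0.8078 |
| 0.02 | 1.0% | 0.0477 | 0.8102 | 0.8156 |
| 0.05 | 2.6% | 0.0443 | 0.8139 | 0.8273 |
| 0.10 | 5.4% | 0.0388 | 0.8204 | 0.8468 |

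The like-for-like gains are 0, 0.5, 1.3 and 2.6 percentage points.

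**3. Check by simulation.** Settings: 82 patients, blocks of six within three cancer types, r = 0.6, 6,000 replicates per setting, and two assumed mixes (42/20/20 and 28/27/27).

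- At R2 = 0 there was no inflation and no gain.
- At R2 = 0.10 the unadjusted model reported a mean standard error of 0.177 to 0.178, against an empirical SD of 0.170 to 0.175.
- At R2 = 0.10 rejection under the null was 0.042 to 0.045. Power was 0.795 and 0.799 without cancer type, against 0.825 and 0.830 with it.

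The direction and rough size agree. The inflation is somewhat below the formula's 5.4%, as expected when incomplete last blocks leave some imbalance.

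**4. Baseline tests.** With k independent tests at 0.05 under correct randomisation, the chance of at least one significant result is 1 − 0.95^k: 40% for k = 10, 54% for 15 and 64% for 20. The article does not give k, and many of its scales are related, so these figures only illustrate how readily chance findings arise.

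**5. Cost of adjustment.** With 82 analysed, a model with intercept, treatment and baseline CWS leaves 79 residual degrees of freedom. Adding a three-level factor leaves 77.

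**The case against.** A reader might infer that the plan excludes cancer type from the model. The text does not support that. The analysis section lists no covariates at all, not even the baseline score on which the sample size depends. This is a condensed article, and a fuller protocol or analysis plan may name the stratification factor. The sample-size paragraph explains a variance correction and is not a full model specification. What can be said is that the one adjustment described is baseline CWS.

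A reader might also infer that the baseline tests stand in for adjustment, or that their results will select covariates. Neither is written. The article only leaves the response to a significant test open.

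Nor does the standard error have to be too large. That requires cancer type both to be omitted and to predict T1 CWS after baseline; at R2 = 0 nothing is lost. The error is conservative, so it cannot produce a false claim of efficacy. Setting the planned power of 0.80 against 0.847 would overstate the gain, because the unadjusted analysis at the same R2 already has 0.820. Balance within cancer type holds at randomisation and may loosen with the expected 20% attrition.

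All of this stands, and it limits the size of the point. It does not rescue the stated purpose of the baseline tests, and it gives no reason against adjusting for a factor already used in the allocation.

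**Conclusion.** The point holds at modest size. On the adjustment that the article describes, the primary treatment estimate is unbiased, and its interval is either right or somewhat too wide. For an assumed residual R2 of 0 to 0.10 the standard error is up to 5.4% too large, and adjustment would add up to 2.6 points of power (normal approximation, 41 per arm; about 3 points in the simulation). These figures rest on the assumed R2, on balance within cancer type among those analysed, and on cancer type not being in the model, which the article leaves unsaid.

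The criticism of the baseline tests needs no such assumption: they are planned in so many words, and they cannot serve the purpose given. As written they change no estimate or interval of the primary analysis, so the harm is limited to misreading chance differences, and to the room left for choosing covariates after the data are seen.

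**What to change.** In the analysis section, state that the T1 ANCOVA and the longitudinal model both include baseline CWS (continuous) and cancer type (three levels) as fixed, prespecified covariates. If the full protocol or analysis plan already says so, confirm it and cite it.

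Replace the chi-square and ANOVA baseline comparisons with a table by arm of means and SDs, or counts and percentages. Add that covariates will not be chosen from baseline p-values.

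The cost is a few sentences and two of about 79 residual degrees of freedom. The sample size of 104 and the data collection do not change.
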